## Abstract

**Background:**

Dental caries is a serious public health issue globally. It is one of the most prevalent chronic disease in children worldwide. An important public health concern is the existence of one or more decayed, missing, or filled tooth surfaces in any primary teeth of preschool children. Early childhood caries (ECC) can be halted with the use of silver diamine fluoride (SDF) solution. Previous research has indicated that it may have a preventive impact in the treatment of ECC. It is well known that 38% silver diamine fluoride (SDF) is helpful at preventing dental caries. On the other hand, there is not enough evidence on SDF’s ability to prevent caries in primary teeth. To date, no well-planned clinical study has been carried out to investigate SDF’s impact on caries protection.

**Objective:**

The study’s objective is to evaluate and compare the efficacy of 12%, 30%, and 38% silver diamine fluoride in preventing ECC in children aged 24 to 72 months in Mangaluru Taluk.

**Methods:**

This is a single-center, randomized, active-controlled, parallel-group pragmatic trial. Children attending preschool in Mangalore Taluk aged 24 to 72 months will be included in the study. There will be three study groups: group 1 will receive 12% SDF semiannually; group 2 will receive 30% SDF semiannually; and group 3 will receive 38% SDF semiannually. After 6 and 12 months, the principal examiner will conduct a clinical examination of the teeth with a visual and tactile assessment. The effectiveness of the various concentrations of SDF will be determined after 12 months.

**Results:**

The research was funded in September 2020, and data collection started in September 2022. As of February 2023, 150 participants have enrolled in the study. The project is still underway, and it is expected to be completed in December 2023.

**Conclusions:**

Uncertainty surrounds the efficacy of 38% SDF in preventing ECC. Consensus-Based Clinical Case Reporting (CARE) guidelines recommending the use of SDF for ECC prevention will be modified if the findings are as expected. Additionally, since the findings will be broadly disseminated, more nations will implement the use of SDF, easing the burden of ECC on the entire world. Future research on the treatment and prevention of ECC will benefit from the study results. If SDF is successful in preventing caries in a classroom or community context, it will mark an important turning point for preventive dentistry.

**Trial Registration:**

Clinical Trial Registry of India CTRI/2020/02/023420; https://tinyurl.com/3ju2apab

**International Registered Report Identifier (IRRID):**

PRR1-10.2196/46144

## Introduction

### Background

Dental caries is a complex, bacteria-driven, chronic, site-specific, and significant process brought on by a physiological imbalance between minerals in teeth and the fluid in plaque [1]. It is a progressive condition that results from the demineralization of dental enamel caused by the acids generated during the metabolism of sugars by cariogenic bacteria [2] and is one of the most prevalent chronic childhood illnesses; in developing nations, many decayed teeth go untreated. The World Health Organization (WHO) estimates that there are an average of 2.4 decaying, missing, and filled teeth per person worldwide. Dental caries continues to be a significant problem in the majority of developed nations, impacting 60% to 90% of school-aged children. In many industrialized nations, there have been encouraging trends in the fight against pediatric dental caries. In India, where more than 70% of the population lives in rural areas with few health services and restorative therapy is expensive, parents tend to neglect their children’s dental needs, leading to untreated dental caries [1].

The term early childhood caries (ECC) has been used to describe the presence of one or more decayed, restored, or missing primary teeth in a child younger than 6 years [3]. The American Dental Association has classified the presence of one or more decayed, missing, or filled tooth surfaces in any primary tooth in a preschool-aged child as a major public health concern. If ECC is not addressed, it may affect a person’s quality of life in terms of dental health, as well as their body weight, growth, attendance at school, and academic achievement. Measures to prevent and treat severe ECC are essential for both general and dental health because it is a major indicator of adult caries [4].

Poor oral health–related quality of life, low BMI, bad scholastic results, and high absenteeism from school are just a few of the harmful impacts of untreated dental caries that can have an impact on physical development. Due to their vulnerability and reliance on their caretakers for both nutritional requirements and mouth cleanliness, children are most at risk of developing dental caries. Dental caries frequently exhibits no symptoms in its early phases, but if left unchecked, it can cause excruciating pain and potentially fatal infections [3].

ECC prevalence varies from population to population. The illness is most prevalent and severe in East Asia, where prevalence rates in children aged 3 years range from 36% to 85%. In India, 44% of children aged between 8 and 48 months have ECC. Despite tremendous advancements in the field of caries control in recent decades, a high prevalence of ECC in young infants has been observed. It is thus a major social concern; disease control can be accomplished if the demographic groups with the greatest needs are identified. The prevalence of ECC overall in India is 49.6% according to an analysis of all included studies. While in Karnataka state, the prevalence of ECC was reported to be 48.79% [5].

The current cost of treating oral diseases, such as dental caries, places a heavy financial burden on both households and health care providers. Additionally, because of the high expense of dental treatment, elderly adults, socially excluded groups, and children living in poverty are more likely to develop oral diseases. Moreover, even if people have access to therapy, the current course of action for children with severe caries includes giving them local anesthesia to ease their pain and worry. Such treatments have been linked to poor oral health, dental anxiety, and a higher risk of dental caries in children’s permanent teeth in later life. In order to prevent and manage caries and encourage health and well-being, new, accessible, and equitable methods are required [6].

Nonrestorative intervention is a potential alternative method for treating caries in primary molars. Silver diamine fluoride (SDF) has been used successfully to stop the progression of carious lesions in people who cannot tolerate invasive treatment, including children, the elderly, people with medical conditions, and people who require additional care and support. Even though the mechanism of action of SDF is debatable, SDF treatment has been shown to support tooth desensitization and to arrest carious lesions through dentinal tubule blockage, cariogenic bacterial death, remineralization of the demineralized tooth, and inhibition of dentinal collagen degradation. Hence, SDF is a cost-effective, reliable, secure, and efficient caries-prevention substance [6].

Japan authorized the use of silver diamine fluoride (SDF) as a medication in the 1960s. It has been used for many years to cure dental caries in China, Australia, Brazil, Argentina, and Australia. The US Food and Drug Administration authorized the first SDF product for use in the country in 2014. Since 1969, SDF has been used to prevent tooth decay in young children’s primary teeth and pit and fissure caries in developing permanent molars, as well as to treat root caries in geriatric patients. In addition to treating caries, SDF is also used to sterilize infected root canals and treat dental hypersensitivity. It can be applied directly to a carious lesion to arrest the spread of caries or to a caries-prone surface to prevent caries [7].

Although some drawbacks of SDF have been reported, such as staining, its safety has been strongly backed by the fact that not a single untoward event has been connected to its use since it was introduced in Japan. Recent Hong Kong–based randomized controlled studies showed that SDF can decrease carious lesions among children, if SDF is administered twice a year at a concentration of 38%. This method is advised because it can arrest caries without leading to excessive staining. However, after 6 months, it was discovered that a single application of SDF at a concentration of 38% was effective in halting dentinal caries in the primary anterior teeth of preschoolers [6].

SDF has the ability to prevent discomfort, sepsis, and the requirement for extractions if applied early, when the cavity is evident but has not yet resulted in permanent pulpal injury. A 38% SDF solution is more efficient than a solution with a lower concentration, and biannual application is superior to annual application. The use of SDF encourages participation and community support from parents who do not seek dental consultation for their children. Additionally, silver-modified atraumatic restorative therapy is an appealing option that improves treatment results. SDF can increase accessibility and equity in dental care, particularly for people from low socioeconomic backgrounds [6].

A study done by Fung and colleagues in 2018 [8] compared 12% and 38% SDF and found that decay was more substantially arrested when using the higher concentration. Neither that report nor the clinical trial registry listing provides the details of product origin. Further, the investigators did not independently verify the concentrations, making it impossible to generalize from their findings. More research is required to completely evaluate the efficacy of SDF and identify the most effective concentration in order to set guidelines. This study will add on to existing literature, as the SDF product used in our study has not been trialed before. The procedure can be used in basic care settings and could ease the population’s burden of untreated tooth decay. SDF has the potential to play a significant role in comprehensive and successful preventative initiatives to achieve the UN Sustainable Development Goals. We hypothesize that both 12% and 30% SDF will have comparable efficacy with 38% SDF.

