### Objective

To assess and compare the effectiveness of 12% SDF, 30% SDF, and 38% SDF for treatment of early childhood caries among children aged 24 to 72 months in Mangaluru Taluk.

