## Methods

### Trial Design and Protocol Development

This is a single-center, randomized, active-controlled, parallel-group pragmatic trial. This clinical trial protocol’s design and report adhere to the SPIRIT (Standard Protocol Items: Recommendations for Interventional Trials) declaration. The trial schedule is shown in Figure 1.

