### Sample Size Estimation

Based on the previous studies, the anticipated proportion of sound occlusal surfaces at baseline that develop into cavitated dentin lesions at the 30-month follow-up is approximately 25% [3].

Sample size calculation was performed with G* Power 3 (Heinrich-Heine-Universität Düsseldorf). Based on a 5% level of significance, power of 80%, effect size of 0.63, and 3 groups, the required sample size is 120, including 40 in each group. Considering a drop-out rate of 20%, the final sample size is 150, as shown by the following equation: final sample size = ND = N / (1 – d), where *N* is the sample size before drop-out, *d* is the expected drop-out rate, and *ND* is the sample size considering drop-out. Thus, ND = 120 / (1 – 0.2) = 120 / 0.8 = 150, and the total sample required for intervention is 150 (50 in each group). The allocation ratio is 1:1:1. The participants are allocated to the 3 groups equally.

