## Discussion

### Principal Aims

The purpose of this single-center, randomized, active-controlled, 3-arm pragmatic trial is to evaluate and compare the efficacy of 12%, 30%, and 38% SDF in preventing early childhood caries in children aged 24 to 72 months. We are using 38% SDF, which is thought of as the standard of care for preventing ECC, in a positive control group to determine if 30% and 12% SDF are superior.

Our hypothesis is that 38% SDF will have a superior effect compared to 30% and 12% SDF in stopping ECC, because it has a fluoride concentration that is much higher (44,800 ppm) than 30% (35,400 ppm) or 12% (14,100 ppm) SDF. The standard of care will be altered if the results are as expected. Because every child who enrolls in the study should have the right to obtain an efficient preventative strategy, there is no negative control group.

In this study, we evaluate the ability of 12%, 30%, and 38% SDF to arrest ECC. The use of SDF solutions in a clinical setting has been deemed safe, and the application process is noninvasive. Despite the fact that the participants in this study are recruited at a young age, few ethical questions have been raised.

In order to examine the efficiency of 12% and 38% SDF in halting dentin caries in the primary teeth of preschool children, Fung et al [8] undertook a randomized clinical experiment. Other recent research indicates that 38% SDF is more effective than 12% SDF. In a clinical trial, Vollú et al [12] compared the effectiveness of 30% SDF and atraumatic restorative treatment in halting dentine caries in the primary molars of preschoolers. Recent research revealed that 30% SDF could stop caries lesions with effects comparable to those of atraumatic restorative treatment.

The findings of this trial, performed in young children who are in good health, may not be generalizable to other populations of children, such as those who require special medical attention or are older, which is a limitation of this study. It will be necessary to perform additional research on the preventive impact of SDF in individuals with special health care requirements. The generalizability of the study will also be limited by the fact that clinical trials in different countries use different parameters for caries assessment.

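### The Background and the Discussion state conflicting primary hypotheses, and the sample size, with no margin, cannot support a conclusion of comparable efficacy

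*Protocol article*

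**What the plan says.** Three statements in the Protocol article bear on what the trial is meant to show.

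- Introduction, Background, closing sentence: "We hypothesize that both 12% and 30% SDF will have comparable efficacy with 38% SDF".
- Discussion, Principal Aims, first paragraph: 38% SDF is used "in a positive control group to determine if 30% and 12% SDF are superior".
- Discussion, Principal Aims, second paragraph: "Our hypothesis is that 38% SDF will have a superior effect compared to 30% and 12% SDF in stopping ECC". The same paragraph adds: "The standard of care will be altered if the results are as expected".

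The other sections do not choose between them. The Objective is neutral: "To assess and compare the effectiveness of 12% SDF, 30% SDF, and 38% SDF for treatment of early childhood caries". Trial Design and Protocol Development names no superiority, non-inferiority or equivalence frame: "This is a single-center, randomized, active-controlled, parallel-group pragmatic trial". Sample Size Estimation reads: "Based on a 5% level of significance, power of 80%, effect size of 0.63, and 3 groups, the required sample size is 120". Statistical Analysis lists ANOVA or Kruskal-Wallis with post hoc tests for continuous outcomes, and a binary logistic regression for arrest. Neither section gives a margin.

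**The concern.** Comparability and superiority are different statistical questions. Comparability needs a margin fixed in advance and a rule for where the confidence interval must lie. Superiority needs a test of difference. A document that hypothesises both leaves the decision rule undefined: a significant result in favour of 38% would agree with the Discussion, and a non-significant one could be presented as agreeing with the Background.

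The consequence attached to the result is equally open. Principal Aims describes 38% as the accepted standard of care and then says that standard will change if expectations are met, without saying which expectation. A win for 38% would leave the standard where it is.

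At stake is what the trial can conclude about the weaker strengths. If a non-significant test has a high chance of occurring even when a lower strength arrests materially fewer lesions, nothing in the design would separate true similarity from lack of information.

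**Working it through.** **1. The plan's own figure.** Inputs from Sample Size Estimation: alpha 0.05, power 80%, effect size 0.63 (metric not stated), 3 groups, drop-out 20%.

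Pairwise two-sided difference test, normal approximation:
n per arm = 2 × [(1.960 + 0.842) / 0.63]² = 39.55, so 40. Then 40 × 3 = 120, and 120 / (1 − 0.2) = 150. The stated figures are reproduced.

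Other difference-test readings do not give 120:

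| Reading of 0.63 | Result |
|---|---|
| One-sided pairwise test | 32 per arm |
| Two-sided t-test, exact | 41 per arm (power at 40 is 79.5%) |
| Pairwise, Bonferroni for 2 comparisons | 48 per arm |
| Pairwise, Bonferroni for 3 comparisons | 53 per arm |
| Three-group ANOVA, f = 0.63 | about 28 to 30 in total |
| Chi-square, w = 0.63, 2 df | 25 in total |

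So the number belongs to a two-sided pairwise test of difference without multiplicity adjustment. If 0.63 is read as Cohen's h, it is a gap of about 29 to 31 points in arrest rate (for example 70% versus 39%).

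**2. Precision for arrest.** The document gives no expected arrest rate, so 50% to 80% is assumed, with one binary result per child and 40 evaluable children per arm.

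95% CI half-width = 1.96 × √[2p(1 − p) / 40]:
- p = 0.5: 1.96 × 0.1118 = 0.219
- p = 0.7: 1.96 × 0.1025 = 0.201
- p = 0.8: 1.96 × 0.0894 = 0.175

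**3. Chance of a non-significant test when a lower strength is worse.** Power = Φ[(d − 1.96 × SE₀) / SE₁], with SE₀ from the pooled rate and SE₁ from the separate rates.

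For 70% versus 55%, d = 0.15:
- 40 per arm: SE₀ = 0.1083, SE₁ = 0.1069, power 0.28, so non-significant 72% of the time.
- 50 per arm: SE₀ = 0.0968, SE₁ = 0.0957, power 0.34, so non-significant 66% of the time.

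Across 38% arrest rates of 50% to 80%, with 40 per arm, a true 15-point deficit is non-significant 68% to 73% of the time.

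**4. Power if comparability were tested properly.** Margins are assumed, as none is given. With truly equal rates and one-sided 2.5%, power = Φ(m / SE − 1.96), SE = √[2p(1 − p) / 40]:

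| Margin m | p = 0.5 | p = 0.8 | Evaluable children per arm for 80% power |
|---|---|---|---|
| 10 points | 14% | 20% | 252 (p = 0.8) to 393 (p = 0.5) |
| 15 points | 27% | 39% | 112 (p = 0.8) to 175 (p = 0.5) |

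The last column is 2p(1 − p) × (1.960 + 0.842)² / m². With 40 per arm, the smallest margin with 80% power is 2.80 × SE, which is 25 to 31 points.

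**The case against.** **Only two statements are labelled hypotheses.** The third gives the purpose of the positive control, and the Objective is neutral. This stands: a reader might count three rival hypotheses, but the text supports two, plus an aim that points in a third direction. The two alone conflict.

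**The plan never says that non-significance will be read as comparability.** Also true. A reader might infer that any result will be declared a success; the document does not say so. What stands is that nothing in it prevents that reading, while one of its two hypotheses invites it.

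**Multiplicity.** A reader might infer an inflated family-wise error from unadjusted pairwise tests. The document does not support that. It names post hoc tests alongside an overall test but no method, that scheme is written for continuous outcomes, and the detail may sit in an analysis plan that is not shown. No error rate can be attributed to the plan.

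**The sizing does not prove what was intended.** The effect-size metric is unstated, and the logistic model for arrest does not list treatment group among its independent variables. The same 40 per arm would also come from a one-sided 2.5% non-inferiority calculation with a margin of 0.63 SD. However, the document calls 0.63 an effect size and mentions no margin, and a margin that wide would not be a credible meaning of comparable. The sentence about altering the standard of care arguably fits comparability better than a win for 38%. So the sizing shows which question the number can serve, not which one the sponsor had in mind, and the choice is the sponsor's.

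**The conflict sits in the Introduction and Discussion.** Recruitment, treatment and data collection are unaffected. That limits the cost of repair; it does not settle the primary inference.

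**Conclusion.** The contradiction is in the current text and needs to be resolved. The sample size matches a test of difference, and without a margin the design cannot support a conclusion of comparable efficacy.

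The size of the gap rests on assumptions the document does not supply: arrest rates of 50% to 80%, margins of 10 and 15 points, one binary outcome per child, and 40 evaluable per arm after the planned drop-out. The lesion-level wording in Statistical Analysis could change the exact values. Full retention of 50 per arm does not change the conclusion: the 70% versus 55% scenario is still missed about two times in three.

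**What to change.** Before unblinding, state one primary hypothesis and use it consistently in Background and Principal Aims.

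**Lower-cost option, matching the existing size.** Prespecify a two-sided test of difference in 12-month caries arrest for 38% versus 12% and for 38% versus 30%. Remove the comparable-efficacy sentence from Background and the clause in Principal Aims about determining whether the lower strengths are superior. Report risk differences with 95% CIs. Add a sentence such as: a non-significant difference will not be interpreted as comparable efficacy.

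**If comparability is the real question.** Keep it, remove the superiority statements, prespecify a justified margin and a confidence-interval rule, and state that the present size has low power for it.

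Under either option, say which result is meant by the statement that the standard of care will be altered.

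Cost: a text amendment and a short prespecified rule, with no change to enrolment (150 children are already in) or to data collection. The downside is that the comparability claim is either given up or made only with an explicit low-power caveat.

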### Objective

To assess and compare the effectiveness of 12% SDF, 30% SDF, and 38% SDF for treatment of early childhood caries among children aged 24 to 72 months in Mangaluru Taluk.

## Methods

### Trial Design and Protocol Development

This is a single-center, randomized, active-controlled, parallel-group pragmatic trial. This clinical trial protocol’s design and report adhere to the SPIRIT (Standard Protocol Items: Recommendations for Interventional Trials) declaration. The trial schedule is shown in Figure 1.

**Figure 1 figure1:**
[figure not shown]
Schedule of enrollment, intervention, and assessment of groups that received 38%, 30%, and 12% silver diamine fluoride.

### Study Setting

The study is being carried out at preschools of Mangaluru Taluk, South India. The dental examinations are performed after receiving confirmation of participation from preschool teachers or caregivers, and informed consent forms (Multimedia Appendix 1) are sent to the parents of the eligible children. Signed parental consent is collected before the intervention starts.

